## Abstract

**Background:**

Around one in ten women will have a miscarriage in their lifetime. Miscarriage is often considered a trivial event by caregivers, but it is associated with a high burden of psychological morbidity, especially during the first 6 months. There is no validated psychological management strategy for women who have had a miscarriage. The MisTher study aims to evaluate the utility of early, short psychological care for women who have had early miscarriage, in terms of anxiety, depression and post-traumatic stress disorder.

**Methods:**

This is a prospective, multicenter, randomized, controlled, superiority study. In total, 932 women who have experienced early miscarriage (spontaneous interruption of pregnancy prior to 14 weeks of gestation) will be randomly assigned to either the intervention or the control group. The intervention consists of 4 teleconsultations of 45 min with a psychologist. All women, regardless of their allocated group, will be encouraged to seek an early consultation with a general practitioner or midwife. The primary endpoint will be anxiety at 3 months after randomization evaluated using State Trait Anxiety Inventory. The secondary endpoints will be anxiety at 6 months evaluated using State Trait Anxiety Inventory, depression at 3 and 6 months evaluated with the Beck Depression Inventory, and post-traumatic stress disorder at 3 and 6 months, evaluated using the Posttraumatic stress disorder Checklist Scale.

**Discussion:**

This project will validate the importance of early psychological management, based on primary care and accessible to most women, via teleconsultation, in reducing the frequency of psychological disorders after early miscarriage. Our results should provide a basis for new recommendations for the management of women who have experienced miscarriage, notably by recommending the involvement of trained psychologists in the management pathway for these women.

**Trial registration:**

The trial is registered with ClinicalTrials.gov: NCT05653414. December 15th, 2022.

## Background

Miscarriage is defined as the spontaneous loss of pregnancy before the foetus has achieved viability. The French national college of gynaecologists and obstetricians (Collège national des gynécologues et obstétriciens) defines early miscarriage as the spontaneous expulsion of an inter-uterine pregnancy at less than 14 weeks gestation [1]. The occurrence of early miscarriage complicates more than 10% of pregnancies [1]. According to Quenby et al., early miscarriage accounts for 15.3% (95% confidence interval (CI) 12.5–18.7%) of diagnosed pregnancies [2]. The prevalence of women who have experienced a miscarriage is 10.8% (95%CI 10.3–11.4%), and overall, it is estimated that 23 million miscarriages occur annually worldwide [3].

Because of its frequency, miscarriage is often considered a trivial event. However, for women who experience miscarriage, it can be a traumatic event associated with grief [4]. In a systematic review by Mergl et al. that included 13 cross-sectional and 8 longitudinal studies totalling 2,597 patients from 11 countries, 17 of the 21 studies observed marked grief in women after a miscarriage or stillbirth [5].

In a paper published in 2016, Markin discusses some common errors made in the treatment of perinatal grief after a miscarriage, including minimizing or avoiding painful affects related to the miscarriage, assuming that the patient’s grief will be resolved in case of a subsequent healthy pregnancy, and neglecting early unresolved losses that are reawakened by the miscarriage [6]. The international literature is in agreement that there is significant psychological morbidity associated with miscarriage. Anxiety, depression and post-traumatic stress disorder PTSD have all been studied in women after miscarriage. According to a review of the literature by Farren et al. in 2018, anxiety is the most common and most persistent psychological disorder after miscarriage [7]. Immediately after a miscarriage, 41% of women present diagnostic criteria for anxiety, with significantly higher scores than in a peripartum control group [8, 9], while at one month after miscarriage, the proportion of women with anxiety was also found to be higher than in a control group [10]. In reported studies, anxiety scores tend to normalize after around 6 months, compared to non-pregnant women [11–13]. However, anxiety may persist up to 12 months after miscarriage, compared to women who had a live birth [7, 14]. Depressive syndrome is diagnosed within 2 weeks after miscarriage in 22 to 36% of women across various studies [8, 12, 15, 16]. Similarly, in women who have had a miscarriage, the relative risk of having a diagnosis of depression was 3 to 4 times higher than in a control group of non-pregnant women [7, 15–17]. The risk of depression is thought to decrease progressively over the first month, although Bergner et al. found that depressive symptoms increased during the first trimester after miscarriage [18]. Finally, PTSD was identified in 25% of women at one month after miscarriage, and in 6% at 4 months in another study [19]. In a study by Farren et al. reported in 2020, at 9 months after a miscarriage, the proportion of women with psychological disorders was 17% for anxiety, 5% for depression, and 16% for PTSD [20].

The psychological troubles associated with miscarriage can have a negative impact on subsequent pregnancies. Fertl et al. reported that women who had a history of spontaneous pregnancy loss had higher levels of anxiety during the first trimester of subsequent pregnancy, compared to women with no history of miscarriage [21]. In a French study by Barbe et al., it was found that during the first trimester of pregnancy, women with a history of spontaneous miscarriage had higher stress levels relating to the medical and obstetric risks or fetal health, than women with no history of miscarriage [22]. Similarly, Haghparast et al. showed that pregnant women who had a history of spontaneous abortion during the previous year had higher scores on anxiety and depression scales (amongst others) compared to pregnant women without a history of spontaneous abortion [23].

The literature surrounding the psychological repercussions of miscarriage does not provide a consensus as to the optimal management of these disorders. A series of articles published in *The Lancet* in 2021 called for a review of data on spontaneous miscarriage, while the accompanying editorial deemed that research into the prevention and management of spontaneous miscarriage should be given priority, including the repercussions for the mental health of the women affected [3]. Similarly, a review of the literature by Coomarasamy et al. concluded that there is a compelling need to screen for psychological difficulties in women who have experienced pregnancy loss [24]. A summary of recommendations also called for the development of strategies to manage the risks associated with miscarriage, notably the mental health consequences [2]. A Cochrane systematic review published by Murphy et al. in 2012 included only 6 randomized, controlled trials that studied non-pharmacological interventions to improve the mental well-being of women who had experienced a miscarriage [25]. The authors concluded that there was insufficient evidence to demonstrate that psychological support was effective after miscarriage, due to the methodological limitations of the studies included (heterogeneity of the psychological follow-up proposed, variation in endpoints, and small sample sizes). In these studies, the psychological interventions studied were heterogeneous, comprising for example a 50-to-60 min psychological consultation or debriefing session [26–28], two to three sessions of one hour of counselling [17, 29], or interventions combining support with self-care advice [26]. Interventions were proposed between 0 and 11 weeks after miscarriage [29, 30], and were delivered by psychologists [27, 28], midwives [26] or specialized nurses [29, 30], either during a consultation or at home. Study endpoints were measured at varying timepoints, ranging from one month [17] to 12 months after miscarriage [29]. The measurement scales used also varied across studies, and included the 12-item General Health Questionnaire (GHQ-12), the Beck Depression Inventory (BDI), the Dyadic Adjustment Scale (DAS) [17], the Hospital Anxiety and Depression Scale (HADS) [27, 28], or the Perinatal Grief Scale (PGS) [31], amongst others. In a systematic review of the literature investigating the effect of interventions to reduce stress, anxiety or depression in pregnant women with a history of miscarriage, San Lazaro Campillo et al. could not find a single study up to 2016 that met their inclusion criteria [32]. Yet, cohort studies and clinical trials suggest that psychological interventions and specific support interventions could improve well-being in women who experience miscarriage, and could mitigate the mental health repercussions on subsequent pregnancies. Barat et al. showed that a 2-hour brief supportive psychotherapy performed during the first 24 h of hospitalization was effective in significantly reducing the frequency of anxiety symptoms (13.5% vs. 60.5%), depressive symptoms (32.4% vs. 71.1%), and grief symptoms (10.8% vs. 65.8%) in the group receiving psychotherapy compared to the control group at four-months of follow-up [31]. A study by Johnson et al. in 2015 suggested that a secondary bereavement intervention on grieving in women who experienced miscarriage at 12–20 weeks gestation promoted women’s ability to cope with early pregnancy loss [33]. A randomized study among 106 Iranian women showed a significant reduction in measures of anxiety (7.9 ± 1.07 vs. 13.79 ± 5.36), stress (9.26 ± 1.25 vs. 18.13 ± 7.66) and depression (7.83 ± 1.05 vs.16.26 ± 11.06) after 8 counselling sessions with mindfulness-based stress reduction techniques, as compared to a control group [34]. At the level of healthcare systems, the World Health Organization (WHO) recommends socioculturally relevant, respectful and dignified care, as well as continuity of care through community-based care providers, such as midwives, to help women deal with pregnancy loss [35].

Currently, in France, there are no specific recommendations for the medical and psychological management of miscarriage in primary care. The regular follow-up of pregnancies with low or no risk of complication can be done by a general practitioner (GP) or midwife [36], but a recent national survey from 2016 showed that in the first 6 months, the majority of women are followed by a gynaecologist in France [37]. The survey further confirmed that insufficient attention is paid to women experiencing psychological disorders during pregnancy. Among women in mainland France who gave birth to a healthy baby, 23.6% reported that they had felt sad, depressed or hopeless for at least 2 consecutive weeks. In 2010, the overall psychological state of French women during pregnancy was described as “quite poor” or “poor” by 8.9% of respondents, yet 93.6% of these women did not have any consultation with a mental health professional; of the remaining women, 1.2% consulted a psychiatrist, and 4.4% consulted a psychologist or psychotherapist. Access to psychiatric or psychological care is difficult in France, and is often associated with high out-of-pocket expenses, even though socio-economically disadvantaged women appear to have the greatest needs in this regard – indeed, the proportion of women suffering from anxiety and/or depression increases significantly with increasing social vulnerability [38]. Against this background, a new law was introduced in France on 7 July 2023, aimed at providing support for couples who experience spontaneous pregnancy loss, by offering reimbursement through the national healthcare system of up to 8 sessions with a psychologist, prescribed by a GP or midwife [39]. So far, this political action has not been followed by a concrete effect in terms of healthcare delivery, since only 5% of practising psychologists are registered with the programme to provide the free care, with the result that out-of-pocket expenses remain high for many women. The law also provides for implementation of a dedicated healthcare pathway, bringing together medical and psychological professionals both in the hospital and the community setting, in a pluridisciplinary approach, to provide enhanced support for women after miscarriage, but roll-out is only due to start in September 2024.

There is thus a compelling need to compile detailed data about the management of psychological disorders in women who have experienced early spontaneous pregnancy loss, especially in France. In this context, the aim of this study is to assess the utility of early, short and accessible psychological care for women who have had an early miscarriage.

## Study objectives

### Study hypothesis

The management in women who have experienced early miscarriage with an early and short psychological care can improve psychological morbidity.

### Primary objective

The primary objective of the study is to establish whether early, short psychological care can improve symptoms of anxiety at 3 months.

### Secondary objectives

The secondary objectives of the study are to establish whether early, short psychological care can improve the following:

Symptoms of anxiety at 6 months.Symptoms of depression at 3 months.Symptoms of depression at 6 months.Post-traumatic stress disorder at 3 months.Post-traumatic stress disorder at 6 months.

## Methods

### Study design

This is a prospective, multicenter, randomized, open, controlled, superiority study.

### Participants

To be included, participants must meet all the following inclusion criteria:

women who have experienced early miscarriage within the previous 30 days, defined as spontaneous loss of pregnancy before 14 weeks’ gestation;whose pregnancy had been confirmed by blood or urine analysis;regardless of whether or not they had undergone medically-assisted reproduction;age > 18 years;who can speak and read French sufficiently well to participate in the study;affiliated to a social security system;and who provide written informed consent for participation.

The exclusion criteria are as follows:

women whose miscarriage is due to ectopic pregnancy;women whose miscarriage is due to molar pregnancy;women with recurrent spontaneous miscarriages (defined according to the WHO criteria as either three or more consecutive miscarriages, or 5 or more miscarriages during the woman’s lifetime (even if she gave birth to a healthy baby between miscarriages));women under any form of judicial protection (e.g. guardianship or curatorship);refusal to provide written informed consent.

### Sample size

The following hypotheses were used to calculate the sample size required for the present study:

A percentage of women with anxiety at 3 months after randomization equal to 22% in the control group (without early psychological care) [20].A percentage of women with anxiety at 3 months after randomization equal to 13% in the intervention group (with early psychological care) (based on the average rate observed in populations with no history of miscarriage).

At an alpha risk of 5% and with power of 90%, in a bilateral situation, the number of subjects needed is 373 per group, i.e. a total of 746 participants. Allowing for 20% of patients lost to follow-up at 3 months after randomization, total accrual of 932 women (466 per group) is planned. Assuming a consent rate of 20%, it is estimated that study information will have to be provided to around 5,000 women in total.

Sample size calculations were performed using NQuery software version 4.0.

### Randomization

Randomization will be performed only after written informed consent has been obtained. Block randomization will be performed using a computer generated randomization algorithm using SAS software (Version 9.4, SAS Institute Inc., Cary, NC, USA). Participants will be assigned to either the intervention group or the control group in a 1:1 ratio, balancing across 2 factors, namely, randomization will be stratified by parity (with vs. without children) and by use of medically assisted reproduction (with vs. without medically assisted reproduction). It is expected that women who have never yet had a live birth and those who become pregnant via medically assisted reproduction may have a more painful psychological experience of miscarriage.

### Recruitment

Recruitment into the study will be performed as follows: Information about the study will be provided through flyers, posters and information leaflets, by the gynaecologists and midwives caring for patients at the time of miscarriage. If the woman accepts to participate, she can contact the clinical research assistant whose contact details are provided on the information leaflet. After verification of the inclusion and exclusion criteria, an inclusion visit will be scheduled with a GP or midwife and will take place by teleconsultation. If, after the inclusion visit, the woman confirms her desire to participate, the informed consent form will be sent to her by post. As soon as the signed informed consent has been returned to the GP or midwife, then the woman is considered to be included in the study, and randomization can take place.

### Study procedures

Randomization will be conducted following return of the signed informed consent form. Following randomization, women will be notified of their allocated group by phone by the GP or the midwife. Within 7 days after randomization, the clinical research assistant will obtain and record study data about the participant and about the miscarriage by phone. During this initial phone call, the STAI Y-A form, as well as the Beck Depression Inventory (BDI) and the Posttraumatic stress disorder Checklist Scale (PCLS) will be completed by the participant.

Two follow-up visits will take place, namely at 3 and 6 months after randomization. These visits will be performed by telephone by the clinical research assistant. For each visit, clinical and demographic data will be recorded (any change in marital status or professional activity, occurrence of any important life events, especially a new pregnancy), and the self-report questionnaires (STAI Y-A form, BDI and PCLS) will be completed again by each participant. Forms may be completed electronically or using paper versions.

### Study interventions

#### Intervention group

Women allocated to the intervention group will have 4 counselling sessions with a psychologist, in addition to the standard of care according to local practice. The first counselling session must be held within 14 days after randomization, and all four counselling sessions must be completed within 2 months after randomization. Each session will last 45 min and will be performed by teleconsultation. The sessions will be based on active listening, expression of emotion surrounding the miscarriage, taking account of each individual’s life circumstances and experiences, and potentially discussing any other important life events that the participant may have found traumatic. Finally, the participants’ resources, possible sources of support and life projects will also be addressed.

#### Control group

Women allocated to the control group will receive standard of care according to local practice.

#### Intervention and control groups

Women in both groups will be encouraged to attend an early consultation with either their GP or a midwife.

### Outcome measures

#### Primary outcome

The State Trait Anxiety Inventory version Y (STAI-Y) consists of two sets of twenty items, which yield scores indicating the level of anxiety the subject has at present (state anxiety, STAI Form Y-A) and the extent to which the person is prone to experience anxiety (trait anxiety, STAI Form Y-B). The Y version was developed to eliminate items that are more specifically bound to depression. In this study, the participants’ feelings of anxiety will be evaluated using the STAI Y-A form (STAI) [40]. The STAI Y-A form only focuses on the psychological, and not the somatic aspects of anxiety. The STAI Form Y-A is a self-reported questionnaire. Each item is scored from 1 to 4 and a sum score of all items is computed. Higher scores indicate greater anxiety. For the purposes of this study, presence of anxiety is defined as a score of 46 or higher.

#### Secondary outcomes

Depression will be evaluated using the Beck Depression Inventory - Second Edition (BDI-II) [41, 42]. The BDI-II is a self-reported index of depressive symptoms experienced in the past 2 weeks. The questionnaire includes 21 items relating to depression symptoms and attitudes. Answers are on a 4-point scale from 0 to 3 (0 = not at all bothered; 3 = severely bothered). The minimum score is 0 and the maximum is 63. Total score indicates that depression is minimal (from 0 to 11 points), mild (from 12 to 19 points), moderate (from 20 to 35 points), or severe (from 36 to 63 points). For the purposes of this study, presence of depression is defined as a score of 19 or higher, i.e. mild, moderate or severe depression.

The possible presence of post-traumatic stress disorder will be evaluated using the Posttraumatic stress disorder Checklist Scale (PCLS) [43]. The PCLS is a short self-report inventory assessing the 3 main syndromes of PTSD, namely intrusion (intrusive feelings and imagery, dissociative-like re-experiencing, flashbacks); avoidance (numbing of responsiveness, avoidance of feelings, situations, and ideas); or hyperarousal (anger, irritability, hypervigilance, difficulty concentrating or sleeping, heightened startling). The PCLS is a questionnaire containing 17 items assessing the intensity of 17 symptoms over the course of the previous month. Responses are ranked from 1 (not at all) to 5 (very often), yielding a total score ranging from 17 to 85. A score of 44 or more identifies PTSD.

#### Clinical data

For all participants, we will record the following data: age, marital status, level of education, occupation, use of psychoactive substances (alcohol, tobacco, cannabis, etc.), personal and family psychiatric history, psychiatric/psychological follow-up (psychiatric hospitalization, psychotropic treatments) and gynecological history (number of pregnancies, number of children, miscarriages (early or not), foetal death, ectopic pregnancy, voluntary interruption of pregnancy, medically assisted reproduction, preterm delivery).

Regarding the miscarriage, the following data will be recorded: whether it was a planned pregnancy, whether the pregnancy was the result of medically assisted reproduction, number of weeks gestation, medical/surgical management for the miscarriage, whether the participant told their entourage about the miscarriage.

### Data analysis

#### Data management

The study will use two distinct databases to separately store research data and contact information. Potentially identifying contact information for the participants, such as name, phone number, and address, will be stored in a separate database unconnected to the research database. In the research database, all participants will be designated by an ID number. Electronic data will be saved on a secure server with restricted access.

#### Statistical analysis

Descriptive analysis will be performed. Quantitative variables will be expressed as the mean ± standard deviation or median (range) and qualitative variables as number (percentage). The primary endpoint (presence of anxiety at 3 months after randomization) will be compared between groups using the chi square or Fisher’s exact test, as appropriate. For the secondary endpoints:

presence of anxiety at 6 months after randomization, depression at 3 and 6 months, and PTSD at 3 and 6 months will also be compared between groups using the chi square or Fisher’s exact test, as appropriate.numerical scores for anxiety at 3 and 6 months, and depression at 3 and 6 months after randomization will be compared between groups using the Student t test.

A p-value of < 0.05 will be considered significant. Statistical analysis will be performed using SAS version 9.4 (SAS Institute Inc., Cary, NC, USA).

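### The two stratification factors are not carried into the planned chi-square and t tests, which stay valid but are slightly conservative and less precise than the design allows

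*Protocol article*

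**What the plan says.** The Randomization section of the protocol article sets a 1:1 block allocation in which "randomization will be stratified by parity (with vs. without children) and by use of medically assisted reproduction". The reason given is that women without a live birth and those who conceived with assisted reproduction "may have a more painful psychological experience of miscarriage". The sponsor therefore expects both factors to be prognostic.

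The Statistical analysis section names the tests outright. "The primary endpoint (presence of anxiety at 3 months after randomization) will be compared between groups using the chi square" or Fisher's exact test. The same tests serve for anxiety at 6 months and for depression and PTSD at 3 and 6 months. The numerical anxiety and depression scores "will be compared between groups using the Student t test". PTSD is compared only as a binary endpoint. No named test uses either stratification factor.

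The Sample size section assumes "A percentage of women with anxiety at 3 months after randomization equal to 22% in the control group" and "A percentage of women with anxiety at 3 months after randomization equal to 13% in the intervention group". It concludes: "At an alpha risk of 5% and with power of 90%, in a bilateral situation, the number of subjects needed is 373 per group".

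The Study procedures section places the initial STAI Y-A, BDI and PCLS in a telephone call up to 7 days after randomization. It describes women being told their group before it describes that call. The Study design section calls the trial open, and the Intervention group section lets the first session take place at any time in the 14 days after randomization.

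**The concern.** Stratified allocation forces the arms to be nearly equal in parity and assisted reproduction. Differences between strata then contribute almost nothing to the real sampling variation of the arm comparison. An unstratified chi-square or t test still counts those differences in its variance. If the strata predict the outcome, the calculated standard error is too large, the test rejects less often than its nominal 5% under the null, and some power is lost. The trial takes the trouble to stratify and then does not collect the benefit. At stake is precision on the primary endpoint and on every secondary endpoint, not the credibility of a positive result.

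**Working it through.** **1. The plan's own figure.** Inputs from the Sample size section: 22% against 13%, two-sided 5%, power 90%. With pooled variance under the null and no continuity correction, the mean rate is (0.22 + 0.13)/2 = 0.175, and

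n = [1.960·√(2 × 0.175 × 0.825) + 1.2816·√(0.22 × 0.78 + 0.13 × 0.87)]² / 0.09²
= (1.0532 + 0.6838)² / 0.0081 = 372.5, so 373 per group.

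This matches the stated number exactly. For 20% loss, 746/0.8 = 932.5, which agrees with 932 up to rounding. The calculation is for an unadjusted comparison of two proportions, so the planned test and the sample size agree with each other.

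**2. What ignoring the strata does, by formula.** The documents give no stratum sizes or rates. Assumptions: 50% without children, 15% with assisted reproduction, the two independent, an overall rate of 22%, and the same odds ratio (OR) for each factor. The stratum shares (neither factor, assisted reproduction only, no children only, both) are then 0.425, 0.075, 0.425 and 0.075.

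The unstratified variance per woman is p(1−p) = 0.22 × 0.78 = 0.1716. The variance that matters under balanced strata is the within-stratum average, Σ wₛpₛ(1−pₛ). The standard error is overstated by the square root of their ratio, R, and the true type I error is 2·[1 − Φ(1.96·R)].

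| OR per factor | Stratum rates | Within-stratum variance | R | Type I error |
|---|---|---|---|---|
| 1.5 | 17.6%, 24.2%, 24.2%, 32.4% | 0.1697 | 1.006 | 4.9% |
| 2 | 14.6%, 25.5%, 25.5%, 40.6% | 0.1661 | 1.017 | 4.6% |
| 3 | 10.9%, 26.9%, 26.9%, 52.4% | 0.1583 | 1.041 | 4.1% |

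**3. The same by simulation.** 746 women, four strata, blocks of 2 (assumed), 10,000 replicates under the null and 6,000 under 22% against 13%. CMH is the Cochran-Mantel-Haenszel test.

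| OR per factor | Null: chi-square / CMH | Power: chi-square / CMH | Calculated / actual SE, null |
|---|---|---|---|
| 1.5 | 0.050 / 0.051 | 0.898 / 0.899 | 1.01 |
| 2 | 0.048 / 0.051 | 0.910 / 0.913 | 1.02 |
| 3 | 0.041 / 0.049 | 0.913 / 0.922 | 1.05 |

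The Monte Carlo error of a null rate is √(0.05 × 0.95/10,000) = 0.002, so formula and simulation agree. The largest power difference is 0.922 − 0.913 = 0.009.

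**4. Why the initial scores cannot simply be added.** With a clean baseline correlated r with the outcome, analysis of covariance multiplies the residual variance by 1 − r². At 373 per arm and a true difference of 0.20 SD, power would rise from 0.78 (t test) to 0.82, 0.88 and 0.97 for r = 0.3, 0.5 and 0.7 (r assumed).

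The scores here come after allocation. Suppose that knowing the allocation, or an early session, lowers the intervention arm's initial score by 0.1 SD (assumed). With equal SDs the adjusted estimate is the outcome difference minus r times the initial difference. At r = 0.5 this is 0.20 − 0.5 × 0.1 = 0.15 SD. Power for 0.15 SD with residual SD √0.75 is 0.66, below the 0.78 of the plain t test. Adjustment would then remove part of the effect under study.

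**The case against.** The strongest defence is that nothing here is invalid. An unadjusted test after stratified randomization can only be conservative, the sample size was computed for exactly this test, and the loss is negligible unless the strata are strongly prognostic. The article says only that these women may fare worse; it gives no rates. An analysis plan that is not shown may also add adjusted analyses. All of this stands as a limit on the size of the point. It does not remove the point, because the article itself names the primary test, and that test leaves out factors that the article chose as prognostic.

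Three stronger readings are tempting and are not supported.

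- A reader might infer that the error bars are wrong in a way that endangers the conclusion. The error runs one way only (standard errors slightly too large, type I error at or below 5%), and it comes only from the strata. Leaving out an initial score costs precision, not validity.
- A reader might infer that several power points are being wasted because the initial scores are ignored. That gain needs a baseline unaffected by allocation, and the Study procedures section does not provide one.
- A reader might count the absence of a named confidence interval or imputation method as part of the fault. An article commonly leaves these to the full protocol or analysis plan, so they are not a finding.

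**Conclusion.** The point holds as a modest, nearly cost-free improvement. The design stratifies on two factors expected to matter, and the named tests ignore them. Under assumed odds ratios of 1.5 to 3 per factor, type I error is about 5.0% down to 4.1%, the standard error is up to about 5% too large, and about 1 power point or less is lost on the primary endpoint. These sizes rest on assumed stratum shares and effects. If the factors turn out not to be prognostic, the loss is nil. There is no inflation of false positives, and 373 per group stands.

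**What to change.** In the Statistical analysis section, and before any outcome is compared by arm:

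- Make the primary analysis, and those of the secondary binary endpoints, stratified by parity and assisted reproduction: a Cochran-Mantel-Haenszel test, or logistic regression on arm and both factors. Report the result as a risk difference (Mantel-Haenszel weighted, or standardised from the logistic model).
- For the anxiety and depression scores at 3 and 6 months, replace the t test by a linear model with arm and both factors.
- Keep the chi-square or Fisher tests and the t tests as sensitivity analyses.
- State that the initial STAI, BDI and PCLS scores are not used for adjustment or imputation as now collected. Allow baseline adjustment only for scores completed before the woman learns her allocation.

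The stratified part costs a sentence or two and a few lines of SAS. Both factors are known at randomization, and no more women are needed. A clean baseline is not free: it would need the initial questionnaires moved ahead of disclosure, which is a change of procedure, and it could not help women already enrolled under a schedule that began in July 2023.
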